## Abstract

**Background:**

Hypertension, a worldwide public health problem, is a major risk factor for cardiovascular and kidney disease, and the medical and economic burden of hypertension is increasing. Auricular acupuncture has been used to treat various diseases, including hypertension. Several studies have shown that auricular acupuncture treatment decreases blood pressure in patients with hypertension; however, the scientific evidence is still insufficient. Therefore, we aimed to perform a randomised controlled clinical trial in patients with prehypertension and stage 1 hypertension to evaluate the effect and safety of auricular acupuncture.

**Methods/designs:**

This on-going study is a two parallel arm, assessor-blinded, randomised controlled trial. Sixty participants with prehypertension and stage 1 hypertension will be recruited and randomly allocated into two groups in a 1:1 ratio. Participants in the auricular acupuncture group will receive auricular acupuncture treatment two times per week for 4 weeks. Participants in the usual care group will not receive any acupuncture treatment during the study period. All participants in both groups will be provided with verbal and written educational materials regarding the dietary and physical activity habits for controlling high blood pressure, and they will self-manage their lifestyle, including diet and exercise, during the study. The primary outcome is the 24-h average systolic and diastolic blood pressure, as measured with an ambulatory monitor. The secondary outcomes are the mean change in the average systolic and diastolic blood pressure during day- and night-time, the circadian rhythm of blood pressure, the mean arterial pressure, the change in blood pressure before and after auricular acupuncture treatment, the EuroQOL-5D (EQ-5D), heart rate variability (HRV), body mass index (BMI) and laboratory examination, including lipid profile and high sensitivity C-reactive protein (hs-CRP). Safety will be assessed at every visit.

**Discussion:**

This pilot multicentre randomised controlled trial will explore the feasibility of further auricular acupuncture research and provide important clinical evidence for the effect and safety of auricular acupuncture on blood pressure in patients with prehypertension and stage 1 hypertension compared with usual care.

**Trial registration:**

Clinical Research Information Service: KCT0000169

## Background

Hypertension, a worldwide public health problem, is a major risk factor for cardiovascular and kidney disease. The prevalence and global burden of the disease are increasing [1]. Stage 1 hypertension is systolic blood pressure (SBP) varying from 140 to 159 mmHg or diastolic blood pressure (DBP) varying from 90 to 99 mmHg, and it is a common form of hypertension. The Seventh Report of the Joint National Committee on Prevention, Detection, Evaluation and Treatment of High Blood Pressure (JNC7) defined prehypertension as SBP of 120 to 139 mmHg and DBP of 80 to 89 mmHg to identify individuals who were associated with a risk of developing hypertension and decrease blood pressure (BP), inhibit the progression of BP to hypertensive levels with age and prevent hypertension through early intervention [2].

The current treatments for hypertension include several classes of antihypertensive drugs and strategies to modify the effect of adverse lifestyles on blood pressure. Non-pharmacological interventions, including weight loss, reduced sodium intake, regular physical activity, smoking cessation, and the moderation of alcohol intake, are recommended [2,3]. Antihypertensive drugs, including angiotensin-converting enzyme (ACE) inhibitors, angiotensin receptor blockers (ARBs), beta-blockers, calcium channel blockers (CCBs), and thiazide-type diuretics, are commonly used [2]. However, it is still controversial whether antihypertensive drug therapy is needed for persons with prehypertension [4,5] and mild hypertension [6,7]. Long-term compliance with lifestyle modifications is also difficult for the patient.

Acupuncture has been widely used to treat various conditions, including cardiovascular disease and hypertension [8]. The mechanisms underlying the BP-lowering effect of acupuncture are associated with the control of BP modulators such as renin [9], aldosterone [10], angiotensin II [11] and endothelin-1 [12], and neurotransmitter modulation such as glutamate, GABA, serotonin and endocannabinoids [13]. Of three high-quality, randomised, controlled trials, two showed a positive effect on BP [14,15], but one trial reported a non-significant BP reduction between the groups [16]. Auricular acupuncture is one type of acupuncture based on the understanding that the external ear represents all parts of the human body, including the internal organs, and provides acupuncture points corresponding to these parts [17,18]. Several articles have evaluated the effect of auricular acupuncture on controlling BP [19-22]. Some studies also reported that the electroacupuncture treatment of auricular acupoints decreased BP in patients with hypertension [23,24]. However, the scientific evidence is insufficient [25]. Most previous studies have some methodological limitations, including low quality of the study design, small sample size, inadequate control groups, and a lack of suitable outcome measures. In addition, there is no clinical trial evaluating the effect of auricular acupuncture on prehypertension. Safe and effective interventions that are able to manage pre/mild hypertension would be desirable. Therefore, more rigorous studies are needed to elucidate the effect and safety of auricular acupuncture on pre/mild hypertension.

In the present study, we aimed to perform a randomised controlled clinical trial in patients with prehypertension and stage 1 hypertension to evaluate the effect and safety of auricular acupuncture compared with usual care. The 24-h ambulatory blood pressure will be used as the primary endpoint. The results derived from this study will also be used to explore the feasibility of auricular acupuncture treatment and calculate the appropriate sample size for a future large clinical trial.

## Methods/design

### Study design

This study is a two parallel arm, assessor-blinded, randomised controlled trial. The trial will be performed at two clinical research centres in Korea in accordance with the Declaration of Helsinki and the Guidelines for Good Clinical Practice: the Korea Institute of Oriental Medicine (Daejeon University Hospital) and Dongguk University Ilsan Oriental Hospital. This protocol was registered with the ‘Clinical Research Information Service’, Republic of Korea, which is a registry in the WHO Registry Network. Eligible participants will be stratified by centre, age, and sex and randomly allocated into one of the two groups (the auricular acupuncture group or the usual care group) at a 1:1 allocation ratio and receive treatment for 4 weeks, with 2 months of follow-up (Figure 1). The evaluation of participants and the analysis of the results will be performed by professionals blinded to the group allocation.

**Figure 1 F1:**
[figure not shown]
A flowchart of the study.

### Participants

#### Inclusion criteria

A total of 60 patients will be recruited through local advertising and from the outpatients of the two hospitals. The eligibility criteria for the study include age 19 to 65 years; prehypertension (SBP of 120–139 mmHg or DBP of 80–89 mmHg) or stage 1 hypertension (SBP of 140–159 mmHg or DBP of 90–99 mmHg) according to JNC 7 criteria; and signed written informed consent. After providing consent, the blood pressure of potential subjects will be measured three times. Patients will be eligible for inclusion in the study if the average of three systolic or diastolic pressure measurements is within the specified intervals.

#### Exclusion criteria

Participants will be excluded if they are experiencing or have a history of the following: currently taking antihypertensive prescription or OTC medication or herb/supplements for controlling blood pressure; secondary hypertension; cerebrovascular or cardiovascular disease history; malignant cancer history; diabetes mellitus requiring medication or insulin injection; disease history, including renal diseases, hepatic diseases, thyroid diseases, active tuberculosis, and other infectious diseases; haemorrhagic diseases or taking anticoagulants; T-needle allergy; local infection at the ear; systemic steroid therapy or immune depressants; medications that may affect blood pressure, such as oral contraceptives, central nervous system depressants or stimulants; pregnant or breast-feeding women or women who plan to become pregnant; the use of traditional Korean medicinal treatment during the last 1 month; or inappropriate for this trial for other reasons, including unwillingness to comply with this study protocol or inability to complete the study-related questionnaires by themselves or with assistance, as decided by researchers.

### Randomisation

Study participants who meet the eligibility criteria will be randomly assigned to two groups (the auricular acupuncture group or the usual care group) at the second visit through central randomisation in a 1:1 ratio. Randomisation will be conducted using a computer-generated random allocation sequence through the stratified block randomisation method of the SAS package (version 9.1.3; SAS Institute, Inc., Cary, NC, USA) by a statistician with no clinical involvement in this trial, and the patients will be stratified by centre, age (19–30, 31–40, 41–50, 51–65 years) and sex.

Allocation concealment will be ensured, as the randomisation code will be released after the participants are recruited into the trial and all baseline measures are taken. The subjects and practitioners will be aware of the allocation arm according to the routine care setting. However, the outcome assessors and the statistician performing the data analyses will be masked to the treatment allocation [26].

### Intervention

#### Auricular acupuncture treatment group

Patients in the auricular acupuncture group will receive auricular acupuncture treatment twice a week for 4 weeks. Auricular acupuncture, which is attached to the skin, will be used for this trial, and Haeng Rim T-needles (Haeng Rim Seo Won Medical Co., Korea) will be adopted for intervention. The acupuncture points were selected by an expert committee composed of professors and researchers who specialise in traditional Korean medicine on the basis of a literature review [20,22] and a textbook [17] about acupuncture for blood pressure. At every visit, after the acupuncture points have been sterilised with 75% alcohol preparation pads, T-needles will be applied to six ear acupuncture points: the ear apex point (HX6, 7i), the endocrine point (CO 18), the *shen men* point (TF4), the superior triangular fossa point (TF1), the heart point (CO15), and the groove of the posterior surface point (PS). Attached T-needles should be maintained for 3–4 days and then removed. In addition, T-needles will be attached on one ear in the first session and the opposite ear in the next session, alternating thereafter.

The auricular acupuncture treatment will be conducted by doctors of Korean medicine who are certified by the Korean Ministry of Health and Welfare with at least 4 years of clinical experience and who have received more than 6 years of oriental medicine college education. They will take a 1-day training course for this trial, and the techniques for auricular acupuncture treatment will be standardised between practitioners. In addition, all study protocols and details, including the recording method for the clinical record form, outcome assessment methods, and monitoring process, will be standardised between the two centres through workshops before the beginning of the study. Additional treatment, including antihypertensive drugs and treatment with traditional Korean medicine, will not be allowed during the trial.

#### Usual care group

Subjects randomised to the usual care group will not be given auricular acupuncture treatment. However, participants in both groups will be provided with verbal and written educational materials regarding dietary and physical activity habits for controlling high blood pressure and self-manage their lifestyle, including diet and exercise, during the study. Additional treatment, including antihypertensive drugs and treatment with traditional Korean medicine, will be prohibited, and any violations will be recorded.

### Outcome

#### Primary outcome measurement

The primary outcome measure is the 24-h mean systolic and diastolic blood pressure. The subjects will undergo 24-h ambulatory blood pressure monitoring (PressureTrak Oscillometric Ambulatory Blood Pressure Monitor, SunTech, Morrisville, NC, USA), and the monitor will be programmed to record blood pressure measurements twice per hour during daytime (7 a.m. to 10 p.m.) and once per hour during night-time (10 p.m. to 7 a.m.). The mean systolic and diastolic blood pressure during the entire 24-h monitoring period will be used in the data analysis.

#### Secondary outcome measurements

We will assess the mean change in the mean systolic and diastolic blood pressure during daytime and night-time. The participants will be instructed to fill out a diary to record the time of sleeping and rising, and the readings will be divided into daytime and night-time values according to individual wake times and bedtimes. In addition to the mean systolic and diastolic blood pressure, the circadian rhythm of blood pressure and the mean arterial pressure will also be evaluated.

The change in blood pressure before and after auricular acupuncture treatment will be assessed. Blood pressure will be observed and recorded at every visit. At every visit, the brachial blood pressure will be measured three times in at least 1-min intervals using an automatic blood pressure monitor (FT-700 R; Jawon medical, Kungsan-city, Korea) with the subjects resting for at least 5 min in a quiet and temperature-controlled room with their upper arm at heart level. Subjects will be instructed not to drink caffeinated drinks such as coffee or tea and not to exercise, smoke, or eat 2 h before the blood pressure test [27]. The mean of these three measurements will be used in the data analysis.

The EuroQOL-5D (EQ-5D) will be used to evaluate health-related quality of life (HRQOL). The EQ-5D questionnaire is the most widely used instrument to measure health status, and it assesses scores across five dimensions of health: mobility, self-care, usual activities, pain or discomfort, and anxiety or depression. Each dimension is divided into three categories: no problems, some problems, and extreme problems. The Korean version of the EQ-5D has been developed, and its validity and reliability have been demonstrated [28].

Heart rate variability (HRV) is a useful non-invasive tool to investigate the sympathetic and parasympathetic function of the autonomic nervous system and cardiac autonomic dysregulation in hypertension. An SA-6000 (Medicore Co. Ltd., Seoul, Korea) will be used for studying HRV. The results, including the standard deviation of all of the normal-to-normal intervals (SDNN), the square root of the mean squared differences of successive normal-to-normal intervals (RMSSD), the percentage of successive normal interbeat intervals greater than 50 ms (pNN50), the very low frequency (VLF), low frequency (LF), high frequency (HF), total power (TP), LF/HF ratio, heart rate, and HRV index, will be analysed at baseline and 5 and 13 weeks after baseline. This test will be performed at DongGuk University Ilsan Oriental Hospital only.

BMI (body mass index) is the most commonly used indicator of obesity and is determined from height and weight. In this trial, BMI will be assessed at baseline and 5 and 13 weeks after baseline.

Laboratory examination will be performed for the lipid profile, hs-CRP, fasting blood glucose, and uric acid. The lipid profile measures total cholesterol, HDL cholesterol, LDL cholesterol, and triglyceride levels. Blood samples will be collected after overnight fasting at baseline and at weeks 5 and 13. An overview of the outcome measurement time points is presented in Table 1.

**Table 1 T1:** Schedule for treatment and outcome measurements

**Period**	**S**	**T**								**F**	
Visit	1	2	3	4	5	6	7	8	9	10	11
Week		1		2		3		4		5	13
Informed consent	●										
Inclusion/exclusion criteria	●										
Random allocation		●									
Auricular acupuncture treatment		○	○	○	○	○	○	○	○		
BP before and after auricular acupuncture treatment		○	○	○	○	○	○	○	○		
24-h ABPM	●					●				●	●
Laboratory examination		●								●	●
BMI	●					●				●	●
EQ-5D		●								●	●
Heart rate variability	●									●	●
Safety assessment		●	○	○	○	○	○	○	○	●	●

*S* Screening period, *T* treatment period, *F* follow-up period, *BP* blood pressure, *ABPM* ambulatory blood pressure monitoring, *BMI* body mass index, *EQ-5D* EuroQOL-5D.

●: Both the auricular acupuncture group and the usual care group.

○: Only the auricular acupuncture group.

### Sample size

There is a growing body of research evaluating the effect of acupuncture for various diseases, including hypertension. However, there is still a lack of studies evaluating the effect of auricular acupuncture on prehypertension or stage 1 hypertension. There is no previous study on which to base the sample size calculation. The current study is designed as a pilot study to determine initial data for the primary outcome measure to perform a sample size calculation for a large-scale randomised controlled trial. Each group will include 30 participants, which is the minimum sample size for evaluating the effect of auricular acupuncture. More than 80% of all eligible patients can be recruited, and more than 80% of all randomised patients have to complete the scheduled treatments, assessments, and follow-up [29-31].

### Statistical analysis

All analyses will be performed with SAS (version 9.1.3; SAS Institute, Inc., Cary, NC, USA) by a statistician blinded to the allocation of groups. Statistical analysis will be undertaken on the intent-to-treat (ITT) basis with a 95% confidence interval using multiple imputations. The ITT analysis will include all patients who are randomised [32], and the per-protocol (PP) analysis will include patients who complete the study and do not have major protocol violations [33]. All analyses will be based on the ITT population, and the result of the ITT analysis will be compared with the PP analysis to assess the sensitivity.

Analysis of covariance (ANCOVA) with the baseline score as a covariate for the whole subject pool will be used to assess differences in treatment outcomes between the two groups at each of these time points as a main analysis. The results for the applicable stratified groups with centre, age, and sex as stratified variables will be assessed as additional analyses. The repeated measures analysis of variance will be performed for the different time point assessments.

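### The main ANCOVA omits the stratification factors (centre, age band, sex), so its confidence intervals may be somewhat too wide, by an amount the protocol does not allow one to fix

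*Protocol article*

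**What the plan says.** The Randomisation section states that "the patients will be stratified by centre, age (19–30, 31–40, 41–50, 51–65 years) and sex", using a "computer-generated random allocation sequence through the stratified block randomisation method". Study design names the same three factors and adds that "The trial will be performed at two clinical research centres in Korea".

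The Statistical analysis section then fixes the main analysis: "Analysis of covariance (ANCOVA) with the baseline score as a covariate for the whole subject pool will be used" to compare the two groups at each time point. The stratification factors appear in the next sentence, outside that model: "The results for the applicable stratified groups with centre, age, and sex as stratified variables will be assessed as additional analyses".

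The Sample size section says "Each group will include 30 participants, which is the minimum sample size for evaluating the effect of auricular acupuncture". It describes the trial as a pilot with no earlier study to base a calculation on, and states no effect size, standard deviation or power.

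**The concern.** Stratified blocks make the two arms more alike on centre, age band and sex than simple randomisation would. If those factors predict the outcome, the treatment difference varies less from trial to trial. A model without them does not credit that gain: their variation stays in the error term and the standard error is overstated. The interval then covers more than 95% of the time and the test rejects less than 5% of the time under the null.

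This is not a detail left to an unseen analysis plan. The article names the main model, names the factors and places them outside it without a reason.

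What is at stake is precision. It matters in a trial of 60, and the more so because the pilot's primary-outcome data are meant to size a larger trial.

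**Working it through.** **Inputs from the protocol article**
- Strata: 2 centres × 4 age bands × 2 sexes = 16 (Study design; Randomisation).
- Patients: 30 per arm, 60 in total, so 60 / 16 = 3.75 per stratum on average (Sample size).
- Allocation: 1:1 in stratified blocks, block size not stated (Randomisation).
- Main model: group plus baseline (Statistical analysis).
- Confidence level: 95%, taken as two-sided 5%.

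The document has no figure of its own to reproduce on this point.

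**Assumptions**
- R² is the share of the baseline-adjusted residual variance explained by centre, age and sex. The document gives no value, so it is varied from 0 to 0.30.
- Block size is taken as 2 or 4.
- Strata have equal expected size, factor effects are additive and unrelated to baseline, and data are complete.

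**Step 1: degrees of freedom.** The baseline-only model has 60 − 3 = 57. Centre (1), sex (1) and age band (3) use 5 more, leaving 52. The critical values are t(57) = 2.0025 and t(52) = 2.0066.

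**Step 2: approximate width ratio, adjusted to baseline-only.** Ratio = √(1 − R²) × t(52) / t(57).
- R² = 0: 1.002
- R² = 0.05: 0.977
- R² = 0.10: 0.951
- R² = 0.20: 0.896
- R² = 0.30: 0.838

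With 48 patients (80% of 60) the ratios barely move: 1.003 at R² = 0 and 0.952 at R² = 0.10.

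**Step 3: simulation.** The formula ignores the small chance correlation between group and factors that incomplete blocks leave behind. A simulation with 4,000 trials per setting includes it. Each cell gives blocks of 2 / blocks of 4.

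| R² | Change in CI width on adding main effects | Type I error, baseline-only | Type I error, main effects added |
|---|---|---|---|
| 0 | +0.9% / +1.2% | 0.049 / 0.049 | 0.048 / 0.051 |
| 0.05 | −1.7% / −1.2% | 0.043 / 0.047 | 0.048 / 0.049 |
| 0.10 | −4.2% / −4.0% | 0.042 / 0.043 | 0.055 / 0.053 |
| 0.20 | −9.9% / −9.7% | 0.030 / 0.039 | 0.049 / 0.057 |
| 0.30 | −15.9% / −15.6% | 0.022 / 0.025 | 0.048 / 0.055 |

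The Monte Carlo standard error near 5% is √(0.05 × 0.95 / 4000) = 0.0034, so the last column is compatible with 5%. The baseline-only model never exceeds 5% and falls below it as R² grows.

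**Step 4: break-even.** Interpolating between R² = 0 and 0.05 gives 5% × 0.9 / 2.6 = 1.7% for blocks of 2 and 5% × 1.2 / 2.4 = 2.5% for blocks of 4. That is 2 to 3% in whole numbers.

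**Step 5: all 16 strata as terms.** This uses 15 degrees of freedom instead of 5. At R² = 0 the interval widens by 3.4% / 5.3%, and break-even comes only near R² = 0.07 to 0.10.

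**The case against.** The strongest reply is that baseline 24-h blood pressure is already in the model and carries part of any age, sex or centre effect. What counts is the variance the factors explain after that, and the document gives no figure for it. At 0 to 5% the interval width changes by only about +1% to −2%, which is negligible. This stands, and it is why the point is conditional.

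Four stronger readings are tempting, and the document does not support them.

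- **The intervals are too wide and power is wasted.** Whether they are too wide depends on an unknown R². No power is stated in this pilot, so there is no benchmark against which power could be wasted.
- **The main result is biased or its type I error inflated.** The error runs the other way: type I error stays at or below 5%.
- **The additional analyses are tiny subgroup comparisons that should be replaced by interaction estimates.** The sentence does not say whether it means stratified or adjusted models or separate subgroup results.
- **The arms will not be 30 and 30.** Incomplete blocks can produce unequal arms, but how often depends on a block size that is not given. It also hardly matters: 27 against 33 keeps 4 × 27 × 33 / 60² = 0.99 of the efficiency of equal arms.

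**Conclusion.** The mismatch is real: the trial randomises within centre, age band and sex, and its main model leaves all three out without a stated reason. The consequence is possible conservatism and some loss of precision. The validity of the main test is not harmed.

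The size cannot be determined from the document. Over an assumed R² of 0 to 0.30, it runs from a trivial loss on adjusting (about 1% in width) to a worthwhile gain (about 16%). The balance favours adjusting, because the possible loss is small and break-even is low. These figures rest on the assumptions listed with the calculation, chiefly complete data, additive effects and blocks of 2 or 4.

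**What to change.** Make the main model: outcome = group + baseline value + centre + sex + age band, using the four bands from the randomisation, as main effects only. Do not fit all 16 strata as separate terms with 60 patients. Keep the baseline-only ANCOVA as a sensitivity analysis. If the sponsor prefers baseline-only as the main model, state why the stratification factors are left out.

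The cost is a short change of wording, no new data, 5 degrees of freedom (57 to 52), and an interval about 1% wider if the factors are not prognostic. The Trial status section reports recruitment still open with 54 patients, and the analysing statistician is to be masked to allocation, so the change can be made and dated before unblinding.
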